### Baseline study visit

As part of the baseline visit, we will collect patient information including age, height, weight, European System for Cardiac Operative Risk Evaluation (EuroSCORE II) [35], smoking and drinking status, diabetes mellitus, peripheral arterial disease, lipid profile, pulmonary and cardio-cerebral co-morbidity, and pulmonary infection during the preceding 30 days. Preoperative hematology and biochemistry assessments will also be performed including full blood count, electrolytes, liver and renal function tests, coagulation profile, thyroid function tests, and C-reactive protein. Enhanced thoracic and abdominal computed tomography will be performed to confirm the preoperative diagnosis, and preoperative transthoracic echocardiography will be used to measure left ventricular function as well as to detect valvular disease or other pathologies that meet the exclusion criteria. Additional clinical and study data will also be collected at baseline, as well as at other study time points (Fig. 1).

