### Sample size calculation

The sample size was calculated based on the primary outcome of our unpublished pilot study (manuscript in preparation), carried out at West China Hospital (Biomedical Ethics Committee approval no. 201824). In this study, we included 76 patients (*n* = 38 in each group), and defined the primary outcome as the abovementioned 30-day composite of operative mortality and major complications. In this pilot study, 13 of 38 control patients (34.2%) suffered the following outcomes: death, 4; paraplegia, 1; postoperative renal failure, 7; severe liver dysfunction, 4; or gastrointestinal complications, 1. A total of 9 of 38 patients in the RIVP group (23.7%) experienced the following outcomes: death, 3; paraplegia, 0; postoperative renal failure, 6; severe liver dysfunction, 1; or gastrointestinal complications, 1. The trial is planned to have 80% test power with a two-sided type I error rate of 5%, assuming a dropout rate of 10% over the course of the entire study. For statistical significance, 636 patients (318 participants in each arm) will be required for this trial according to the following statistical formula not including the 76 patients in the pilot study:$$ \mathrm{n}=\frac{{\left({Z}_{1-\alpha /2}+{Z}_{1-\beta}\right)}^2\left[{p}_1\left(1-{p}_1\right)+{p}_2\left(1-{p}_2\right)\right]}{\delta^2} $$

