### Data analysis

All patients will be analyzed according to the intention-to-treat protocol. Data analysis will be performed by a statistician using SPSS 20.0 (IBM, Chicago, IL, USA). Differences associated with *p* < 0.05 will be considered statistically significant. Continuous variables will be expressed as mean ± standard deviation or median (interquartile range), and differences in such variables will be analyzed using an independent *t* test or the Wilcoxon signed-rank test, depending on whether data are normally distributed. Categorical variables will be described as numbers (percentages), and differences in such variables will be analyzed using a *chi-square test* and *Fisher’s exact test*. *Kaplan-Meier* curves and *log-rank* analysis will be used to compare inter-group differences in primary and secondary outcomes. Univariate and multivariate logistic regression will be performed to determine relative risk of primary and secondary outcomes in the RIVP group compared with the control group.

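### The binary primary composite gets several tests at p < 0.05 with none named as decisive; one covariate-adjusted risk comparison should be fixed in advance

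*Protocol article*

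**What the plan says.** Three statements in the Data analysis section of the protocol article reach the primary outcome.

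- On categorical variables: "Categorical variables will be described as numbers (percentages), and differences in such variables will be analyzed using a" chi-square test and Fisher's exact test. The primary outcome in Study outcomes is a yes/no composite, so it falls here.
- On Kaplan-Meier and log-rank: this "analysis will be used to compare inter-group differences in primary and secondary outcomes".
- On regression: "Univariate and multivariate logistic regression will be performed to determine relative risk of primary and secondary outcomes". No covariates are listed.

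One threshold, p < 0.05, applies to every difference, and no method is given priority.

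The Sample size calculation section rests on a single comparison of two proportions: "The trial is planned to have 80% test power", with a "two-sided type I error rate of 5" percent. Its rates come from the pilot: "13 of 38 control patients (34.2%) suffered the following outcomes" and "A total of 9 of 38 patients in the RIVP group (23.7%) experienced the following outcomes".

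Baseline study visit lists the "European System for Cardiac Operative Risk Evaluation (EuroSCORE II") among the data collected, and Study design names five centres.

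**The concern.** A superiority trial needs one result that decides the claim. Here a single hypothesis receives several p-values that can disagree, and the text does not say which counts. The stated 5% error rate and 80% power belong to one of them, the unadjusted comparison of proportions, and the analysis section never names that one as primary. The multivariate model adds the most freedom, because its result depends on covariates still to be chosen.

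Two further problems sit in the same section. The effect measure is mislabelled, since logistic regression yields odds ratios and the outcome is too common for the two to agree. And applying Kaplan-Meier and log-rank to all secondary outcomes includes some that are not suited to it.

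**Working it through.** **Inputs from the protocol article.** p1 = 13/38 = 34.2%, p2 = 9/38 = 23.7%, two-sided alpha 5%, power 80%, dropout 10%, 318 per arm (Sample size calculation); pilot deaths 4/38 in controls and 3/38 with RIVP (same section).

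**1. The plan's own figure.** With the article's formula:

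n = (1.960 + 0.842)² × [0.342 × 0.658 + 0.237 × 0.763] / 0.105² = 7.849 × 0.4059 / 0.011025 = 288.9, so 289 per arm.

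289 × 1.1 = 317.9, so 318 per arm and 636 in total. The stated size is reproduced exactly, and it is the size for an unadjusted comparison of two proportions. After 10% dropout, 318 × 0.9 = 286 per arm are evaluable.

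**2. Several tests on one outcome.** Simulation of 8,000 trials per row, 286 per arm. Assumptions not in the documents: one standard-normal prognostic covariate with log-odds 0.5, 1.0 or 1.5 per SD; event times exponential with mean 5 days; complete follow-up to 30 days. Under the null both arms have 13/38. Simulation error is about 0.24 points at 5%, from √(0.05 × 0.95 / 8,000).

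False-positive rate (%):

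| Log-odds per SD | Chi-square | Log-rank | Adjusted logistic | Any of five tests | Any, without adjusted model |
|---|---|---|---|---|---|
| 0.5 | 5.0 | 5.0 | 5.0 | 6.4 | 5.5 |
| 1.0 | 5.1 | 5.2 | 5.1 | 7.4 | 5.7 |
| 1.5 | 4.8 | 4.9 | 5.1 | 7.8 | 5.5 |

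The other two tests are Fisher (4.1-4.2% alone) and univariate logistic regression, whose rejection rate equalled that of chi-square in every row. Each test alone holds its level. The excess comes from having a choice, and the adjusted model supplies most of it: 0.9 of 1.4 points, 1.7 of 2.4, and 2.3 of 2.8. The simulated covariate was fixed in advance. Free selection of covariates was not simulated and could add more.

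**3. Power of one pre-specified adjusted test.** Same set-up with 34.2% against 23.7%:

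| Log-odds per SD | Chi-square | Log-rank | Adjusted logistic |
|---|---|---|---|
| 0.5 | 79.9 | 79.6 | 81.4 |
| 1.0 | 79.4 | 79.3 | 85.6 |
| 1.5 | 80.0 | 79.6 | 90.5 |

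Simulation error is about 0.45 points. The normal-approximation power of the unadjusted test at 286 per arm is 79.2%.

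**4. Odds ratio against relative risk.** At the pilot rates RR = 0.237 / 0.342 = 0.69, and OR = (0.237/0.763) / (0.342/0.658) = 0.60. Read as a relative risk, the odds ratio would show a 40% reduction where the true figure is 31%.

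**5. Kaplan-Meier and log-rank on the secondary outcomes.** Study outcomes states these as proportions of patients. Death is not part of them, so plain Kaplan-Meier would treat a death as censoring; in pilot controls that is 4/38 = 10.5% of patients. Intubation beyond 48 hours is a status reached at a fixed threshold, not an event with its own onset time.

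**The case against.** **The article is condensed and an analysis plan may exist.** This stands for detail such as the covariate list, whose absence alone would be no finding. But the section is not silent: it assigns parallel tests to the primary outcome under one threshold, and an analysis plan could repair that only by overriding it.

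**The sample size section points to the unadjusted comparison as the main one.** A fair inference, and nothing in the article says that any positive test suffices. The 6.4-7.8% is therefore conditional on such use.

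**The number of tests is easily overcounted.** This also stands. Fisher's exact test is normally kept for sparse tables, and univariate logistic regression nearly duplicates chi-square. In practice there are three distinct analyses: unadjusted, log-rank and adjusted. A reader might compute 1 − 0.95⁵ = 22.6% for five tests, but that assumes independence, and these tests share the same events.

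**Log-rank is defensible for the composite.** A reader might infer that it is invalid there because onset times are missing or death competes. The article does not support that. Monitoring of adverse and clinical events says that event timing is followed until discharge, most components can be dated, and death is inside the composite. In the simulation log-rank held 5% and matched chi-square for power. What remains is that log-rank is not the comparison the trial was sized on.

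**Adjustment is a choice, not a necessity.** Correct. One unadjusted risk comparison matching the sample size section would also remove the multiplicity. The article already plans a multivariate model, so prognostic data are not ignored; that model simply has no defined role or content.

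**Conclusion.** The point holds, at moderate size. The article puts chi-square (or Fisher), log-rank and two logistic analyses on one binary primary outcome at p < 0.05 and makes none decisive. If any positive result could carry the claim, type I error is about 6.4-7.8%, under the assumed covariate strengths and event times. With the unadjusted tests and log-rank only, it is about 5.5-5.7%. The mislabelling of odds ratios as relative risks is certain and would matter at these event rates. The objection to Kaplan-Meier and log-rank is limited to non-fatal secondary outcomes.

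The sample size is not in question: 636 is reproduced and need not change. The gain from adjustment, from about 79% to about 81-86% power, assumes a score with log-odds of 0.5-1.0 per SD. The documents give no figure for how well EuroSCORE II predicts this composite, and centre was not part of the simulation.

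**What to change.** - **Primary analysis.** Name one, at two-sided 5%: the composite as a binary outcome in a logistic model with treatment, centre and EuroSCORE II. Fix the covariate set in advance with nothing optional, and state that the test of the treatment term decides the claim.
- **Effect measure.** Report the standardized risk difference and standardized relative risk from that model, with confidence intervals. Call any odds ratio an odds ratio.
- **Supportive analyses.** Label the unadjusted chi-square test and the log-rank test on the composite as supportive, and keep Fisher's exact test for sparse tables.
- **Secondary outcomes.** Compare non-fatal outcomes as proportions, or use competing-risk methods where timing matters.

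If the sponsor prefers no adjustment, a single unadjusted risk difference or relative risk matching the sample size section also cures the multiplicity but forgoes the power gain.

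The cost is wording in the analysis section before unblinding and slightly more analysis work. A favourable supportive test can then no longer carry the claim.

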**Methods:**

This study is designed as a multicenter, computer-generated, randomized controlled, assessor-blind, parallel-group study with a superiority framework in patients scheduled for TARS. A total of 636 patients will be randomized on a 1:1 basis to a moderate hypothermia circulatory arrest (MHCA) group, which will receive selective ACP with moderate hypothermia during TARS; or to an RIVP group, which will receive the combination of RIVP and selective ACP under moderate hypothermia during TARS. The primary outcome will be a composite of early mortality and major complications, including paraplegia, postoperative renal failure, severe liver dysfunction, and gastrointestinal complications. All patients will be analyzed according to the intention-to-treat protocol.

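### Logistic regression is named as the source of the relative risk, but it yields an odds ratio, and at the planning rates the two differ (0.60 against 0.69)

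*Protocol article*

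**What the plan says.** The last sentence of the Data analysis section fixes both a model and an effect measure: "Univariate and multivariate logistic regression will be performed to determine relative risk of primary and secondary outcomes in the RIVP group", compared with control. Nothing else in the article names an odds ratio, a log-link model, or a step that turns an odds ratio into a risk ratio. The same section plans chi-square and Fisher tests for categorical variables, shows them as counts with percentages, and adds Kaplan-Meier curves with log-rank tests.

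The expected size of the primary outcome is given under Sample size calculation. In the pilot study "13 of 38 control patients (34.2%) suffered the following outcomes", against 9 of 38 (23.7%) in the RIVP group. From these rates, with "80% test power with a two-sided type I error rate of 5" per cent and "assuming a dropout rate of 10% over the course of the entire study", the article concludes that "636 patients (318 participants in each arm) will be required for this trial".

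**The concern.** The model and the measure do not match. Logistic regression works on the log-odds scale, so exponentiating the treatment coefficient gives a ratio of odds. For a rare event the odds and the risk are nearly equal, and the distinction can be ignored. Here about a third of control patients are expected to have the event, so it cannot.

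Relative risk is the only between-group effect measure that the Data analysis section names; the other entries are tests, curves or descriptive summaries. If the sentence were followed literally, the odds ratio would be printed under the name relative risk. Readers who took the label at face value would see a larger effect than the trial found. The Objective and hypothesis section says that the results should support future clinical recommendations, so the size of the effect matters as well as its significance.

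**Working it through.** **Inputs** (Sample size calculation): control 13/38, RIVP 9/38, two-sided alpha 0.05, power 80%, dropout 10%.

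**The plan's own figure first.** With the article's formula and the rounded rates:

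- variance term: 0.342 × 0.658 + 0.237 × 0.763 = 0.2250 + 0.1808 = 0.4059
- n = (1.960 + 0.842)² × 0.4059 / 0.105² = 288.9, rounded up to 289 per arm
- 289 × 1.10 = 317.9, rounded up to 318 per arm, 636 in total

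The stated 636 is reproduced. The calculation compares two proportions and does not depend on which ratio is later reported.

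**The two effect measures at the same rates.**

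- Relative risk = (9/38) / (13/38) = 9/13 = 0.692, a 31% reduction in risk
- Odds ratio = (9/29) / (13/25) = 225/377 = 0.597, a 40% reduction in odds
- Link between them: OR = RR × (1 − p_control)/(1 − p_RIVP) = 0.692 × (25/38)/(29/38) = 0.692 × 25/29 = 0.597

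Models fitted to the 76 pilot records (outcome and arm rebuilt from the counts) agree: the logistic model returns 0.597 and a log-link Poisson model returns 0.692.

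**What misreading would do.** Taken as a relative risk, 0.597 applied to 34.2% implies an RIVP risk of 0.342 × 0.597 = 20.4%, a difference of 13.8 points and a number needed to treat of about 7. The planning rates give 34.2 − 23.7 = 10.5 points and 38/4 = 9.5.

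**How the gap depends on the event rate.** With the relative risk held at 0.692 (control rates other than 34.2% are assumptions):

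| Control rate | Odds ratio |
|---|---|
| 5% | 0.68 |
| 10% | 0.67 |
| 20% | 0.64 |
| 34.2% | 0.60 |
| 50% | 0.53 |

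Pilot components of the composite show the same pattern. Death (4 against 3) gives a relative risk of 0.75 and an odds ratio of (3/35)/(4/34) = 0.73. Renal failure (7 against 6) gives 0.86 and (6/32)/(7/31) = 0.83.

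**The case against.** The best defence is that the term relative risk is used loosely for an odds ratio. If so, the error is one of labelling, and nothing is overstated once the label is corrected at reporting. Logistic regression can also lead to a relative risk, by averaging its predicted risks over the sample, and a full protocol or analysis plan might contain that step. In addition, the primary outcome will be shown as counts and percentages per arm, so a reader can work out the true relative risk. These arguments make the harm conditional and lower the severity. They do not rescue the sentence, which pairs a model with a measure that it does not give directly and mentions no conversion.

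Several stronger readings are tempting but not supported:

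- **That the trial will report an inflated benefit.** This follows only if the odds ratio is published or read as a relative risk. The distortion is away from 1 in either direction, so a harmful effect would be exaggerated too.
- **That every secondary outcome is affected.** The Background section cites stroke at 6.7–10% under the control strategy, where the gap is slight. It cites acute kidney injury at 19–54%, but the secondary outcome is the narrower injury not requiring dialysis, so that range is only a guide.
- **That the missing risk difference contradicts the sample size.** The formula compares two proportions, and so does the planned chi-square test. An article may leave further estimates to the full plan.

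**Conclusion.** The point holds as a moderate one. As written, the Data analysis section attributes a relative risk to a model whose direct output is an odds ratio, for a primary outcome too common for the two to be interchangeable. At the planning rates the values are 0.69 and 0.60, an apparent reduction of 40% in place of 31% if the label is taken literally. The p-value, type I error, power and sample size stand.

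The figures rest on pilot rates from 76 patients, which are imprecise: the 95% CI for the pilot relative risk runs from 0.34 to 1.42. They illustrate the gap and do not predict the trial's result. They are also unadjusted. The multivariate odds ratio depends on covariates that the article does not list, so no adjusted figure can be given.

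**What to change.** Name a method that estimates the relative risk for the primary outcome and the common secondary outcomes. Log-binomial regression, Poisson regression with robust variance, or standardisation of the logistic model over the sample would each do. If logistic regression is kept as a result in its own right, call the exponentiated coefficient an odds ratio. Relabelling alone would remove the false statement, but the trial would then no longer report the measure that it says it wants. An absolute risk difference with 95% CI is a sensible companion, offered as an improvement and not as a correction.

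The cost is one reworded sentence and one different model or post-estimation step. The team should confirm that its chosen method is available in the SPSS version named in the article. No new data are needed, and recruitment and sample size do not change. If RIVP is beneficial, the reported ratio will lie closer to 1 than the odds ratio would.

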### Timeline

2018–2019: Development of research strategy and study protocol.2019–2021: Recruitment and treatment of patients in RIVP-TARS trial.2021–2022: Completion of follow-up and data analysis.

## Discussion

### Trial rationale

Improvements in CPB strategies, including selective cerebral perfusion and temperature management, have led to lower incidence of neurological dysfunction and other complications during the period of circulatory arrest than with DHCA. However, few studies have examined CPB improvement strategies aimed at visceral and lower-body perfusion. We and others propose that maintaining the continuity of lower-body blood flow may be important for avoiding visceral organ dysfunction and postoperative mortality [42, 43].

Distal perfusion through the descending aorta or femoral artery has previously been used to minimize damage to organs [44, 45]. However, this technique is associated with risk of poor occlusion, which seriously interferes with the operating field and leads to false lumen perfusion during femoral artery cannulation. Increasing perfusion through the inferior vena cava may help preserve visceral function and improve TARS outcomes, especially since the viscera lack venous valves.

Our trial will combine ACP and RIVP during TARS using independently controlled upper- and lower-body perfusion circuits. This trial is expected to provide up-to-date data on the safety and efficacy of RIVP in patients undergoing TARS and has the potential to reduce the incidence of circulatory-arrest-associated complications and perioperative blood product transfusion in patients with AAAD, ultimately improving long- and short-term prognosis.

### Trial status

We have completed the eCRF system. The study opened to patient recruitment in January 2019. Completion of this trial is expected on 31 December 2021.

## Abbreviations

AAAD: Acute type A aortic dissection
ACP: Selective antegrade cerebral perfusion
CONSORT: Consolidated Standards of Reporting Trials
CPB: Cardiopulmonary bypass
CRF: Case report form
DHCA: Deep hypothermic circulatory arrest
eCRF: Electronic case report form
EuroSCORE II: European System for Cardiac Operative Risk Evaluation II
FiO_2_: Fraction of inspired oxygen
HCA: Hypothermic circulatory arrest
ICU: Intensive care unit
MHCA: Moderate hypothermic circulatory arrest
MI: Myocardial infarction
PaCO_2_: Partial pressure of carbon dioxide
PaO_2_: Partial pressure of oxygen
RCP: Retrograde cerebral perfusion
RIVP: Retrograde inferior vena caval perfusion
RRT: Renal replacement therapy
SPIRIT: Standard Protocol Items: Recommendations for Interventional Trials
TARS: Total aortic arch replacement surgery
